### Interventions

#### Standard anesthetic management

On the day of operation, patients will be admitted into the operating room to be randomly assigned into either the sevoflurane-remifentanil or propofol-remifentanil group. Vital signs including electrocardiography (ECG), blood pressure (BP), heart rate (HR), pulse oxygen saturation (SpO2), end-tidal carbon dioxide (ETCO_2_), body temperature, and urine output will be monitored throughout the study. 100% fraction of oxygen will be provided by mask to the patients for preoxygenation for 5 min prior to anesthetic induction. No premedication will be given.

All patients will be induced with 0.3 μg/kg sufentanil, 2–2.5 mg/kg propofol, and 0.7–0.8 mg/kg rocuronium or cisatracurium. After tracheal intubation, mechanical ventilation will be established, at a tidal volume of 8-10 ml/kg, respiratory rate of 12–15/min, inspiratory:expiratory ratio of 1:2, fraction of inhaled fresh oxygen as 60%, and flow rate of fresh gas as 1.5 L/min. After induction, anesthesia will be maintained according to one of the two group allocations: (1) 6-8 mg/kg propofol with 0.05–0.2 μg/kg remifentanil for the propofol group or (2) 1.3–1.5 Minimum Alveolar Concentration (MAC) sevoflurane with 0.05–0.2 μg/kg remifentanil for the sevoflurane group. The dosage of anesthetic will be adjusted according to the bispectral index (BIS) value, which will be maintained between 40 and 60. 0.5% ropivacaine 1 to 2 mL for each injection point will be used for scalp nerves block before the start of surgeries. Sufentanil 5–10 mcg can be given, by anesthesiologist discretion, to alleviate potent stress responses when head pins are placed or scalp incision is performed, based on the hemodynamic parameters. Additional sufentanil bolus at the dose of 5-10mcg during operation is allowed, the last bolus should be given ahead of at least 60 min before expected end of surgery. The muscle relaxant cisatracurium will be infused at 0.1 mg/kg/h during the operation for all patients and stopped once the bone flap is secured. Propofol and sevoflurane will be reduced according to BIS and hemodynamic parameters once the bone flap is fixed and stopped at skin dressing.

At the end of the operation, ondansetron 4 mg will be prophylactically administered to all patients to prevent nausea and vomiting, and tramadol 1.5-2 mg/kg will be given if patients are experiencing rigors/chills. Neostigmine 20-40mcg/kg and atropine 0.5-1 mg will be available to antagonize residual muscle relaxation when deemed necessary by train-of-four (TOF) twitch monitoring. Peripheral nerve stimulator will be performed for TOF monitoring, achieving TOF ratio of 1.0 at the ulnar nerve/adductor pollicis is considered an adequate sign of recovery from muscle relaxant.

Adverse hemodynamic responses will be recorded and classified as hypertension, hypotension, tachycardia, or bradycardia, which require standard treatment according to the protocol (Table 2). These episodes of blood pressure and heart rate changes and the medication administered during their treatment will be recorded as “hypertension” (MAP > 20% above preoperative baseline value) or “hypotension” (MAP < 20% below preoperative baseline value), Tachycardia and bradycardia are defined as HR > 100 bpm and HR < 45 bpm, respectively. Standard treatment for hemodynamic disturbances are shown in Table 2.

**Table 2 Tab2:** Treatment for hemodynamic disturbances

Hemodynamic Fluctuation	Definition (if any of the below changes are sustained for equal and/or longer than 5 min)	Standard Treatment Algorithm
Hypertension Episode	MAP > 20% above preoperative baseline	Increase propofol or sevoflurane concentration according to BIS, increase remifentanil infusion rate, or administer 5mcg sufentanil; if correction still not achieved, nicardipine will be given as bolus and/or infusion
Hypotension Episode	MAP < 20% below preoperative baseline	Decrease propofol or sevoflurane concentration according to BIS, give adequate volume loading; if correction still not achieved, vasoactive agent administration (dopamine, norepinephrine, or phenylephrine) will be given with the dose and infusion rate adjusted according to the blood pressure response
Tachycardia Episode	HR > 100 bpm	Esmolol bolus and/or infusion according to heart rate response
Bradycardia Episode	HR < 45 bpm	Atropine administration

*MAP* mean arterial pressure, *HR* heart rate, *bpm* beat per minute

Patient-controlled intravenous analgesia (PCIA) will be used for postoperative pain control with 100mcg sufentanil and 16 mg ondansetron diluted to a total volume of 100 ml within normal saline being prepared, with a bolus dose set at 0.5 ml, a lockout time set at 15 min, and a background infusion of 2 ml/h. PCIA will be started after the patient is discharged from the operating room.

#### Anesthesia monitoring

Anesthesia management will aim to achieve targeted physiological parameters. The blood pressure will be monitored by radial artery catheter placement, and the target value is defined as the range of ±20% of the baseline MAP value, which is defined as the average MAP of the first three values measured after the patient enters the operating room and before induction. When the blood pressure is out of this range, measures will be taken such as changing the infusion rate of crystalloid or colloid and remifentanil, or giving bolus injection of sufentanil or vasoactive agent (such as 0.5 μg/kg/min phenylephrine or 0.01 μg/kg/min norepinephrine). Heart rate will be maintained between 50 and 90 beats per minute. SpO2 will be kept ≥98% during the operation. End-tidal CO_2_ will be maintained between 30 and 35 mmHg by adjusting ventilation parameters. Core body temperature will be kept between 36 and 37 degree Celsius. Plasma glucose concentration will be maintained between 5.0–7.8 mmol/L.

### Discontinuation criteria

#### Massive hemorrhage or massive transfusion

Massive intraoperative bleeding can occur, and this study defines massive bleeding as blood loss exceeding the entire blood volume within 24 h from the start of operation or 50% of circulating blood volume loss within 3 h during operation requiring emergency intervention. Intraoperative massive transfusion (transfusion of more than 10 units of packed red blood cells) may be needed if massive hemorrhage is encountered. If bleeding occurs to this extent and meets either or both of the above criteria, the trial will be discontinued for this particular patient.

#### Anaphylaxis during the operation

Anaphylaxis rarely but occasionally occurs intraoperatively, especially in the setting of antibiotic and muscle relaxant administration, but also with the administration of other medications, and normally can be treated quickly. If such a reaction occurs and is severe, necessitating discontinuation of the operation, the patient will be withdrawn from the trial. Anaphylaxis will be reported as an adverse event.

#### Venous air embolism

Significant venous air embolism has been observed in rare cases, but neurosurgery carries the potential risk for this sometimes intractable complication, especially when the operative intervention occurs near venous sinuses or in the sitting position [12–14]. Venous air embolism may result in severe hypoxia and hypotension which can impair cerebral perfusion and oxygenation. If this happens, timely intervention and resuscitation needs to be carried out and the patient will be withdrawn from the trial. This will be reported as an adverse event.

#### Postoperative coma

If the patient is in a coma (nonresponsive) after operation for any reason, the subject will not be able to cooperate with any neurological assessment, the subsequent follow-up will need to be discontinued, and this will be noted in the neurologic complication section. The patient will be withdrawn from the trial.

#### Outcomes

Patients will have been screened 1 to 2 days before operation, and the demographic characteristics, clinical manifestations, and past history obtained at this time. Detailed descriptions of the lesion in MRI will be obtained. The lesions’ pathologic diagnoses will be obtained 2 weeks after the tumor removal. Neurologic function will be assessed using the National Institute of Health Stroke Scale (NIHSS/mNIHSS) at baseline and in the postoperative period. NIHSS scores 15 items including consciousness, visual function, facial and motor function, ataxia, sensory and language function, and attention, and the total score ranges from 0 (no deficit) to a maximum of 42. A modified version of the NIHSS (mNIHSS) abridges to 11 items by deleting level of consciousness, facial palsy, limb ataxia, and dysarthria; the sensory item is collapsed from 3 to 2 choices [15]. Since there is no reliability and validity evidence comparing NIHSS and mNIHSS use in the intracranial tumor population, we will score both as primary outcomes in this study. The scoring system is shown in appendix. Mini-mental state examination (MMSE) will be used to assess the cognitive performance of patients at baseline and after operation. During anesthesia recovery, Anesthesia Recovery Quality and the modified Aldrete scale will be used to assess the recovery condition of patients. Visual Analog Scale (VAS) will be used to assess postoperative pain. QoR-40 (Quality of Recovery from Anesthesia) will be used at 2 days after operation to assess the recovery condition and the satisfaction of the patient related to anesthesia. All adverse events will be recorded. The schedule of data collection is shown in Fig. 1.

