**Methods:**

This is a prospective, single-center, randomized parallel arm equivalent clinical trial, which is approved by China Ethics Committee of Registering Clinical Trials (ChiECRCT-20,160,051). Patients with supratentorial gliomas diagnosed by magnetic resonance imaging will be eligible for the trial. Written informed consent will be obtained before randomly assigning each subject to either the sevoflurane-remifentanil or propofol-remifentanil group for anesthesia maintenance to achieve an equal-desired depth of anesthesia. Intraoperative intervention and monitoring will follow a standard anesthetic management protocol. All of the physiological parameters and other medications administered during the intervention will be recorded. The primary outcome will be neurologic function change assessed by National Institute of Health Stroke Scale (NIHSS) within 4 h after general anesthesia when observer’s assessment of alertness/sedation (OAA/S) reaches 4. Secondary outcomes will include NIHSS and modified NIHSS change 1 and 2 days after general anesthesia, hemodynamic stability, intraoperative brain relaxation, quality of anesthesia emergence, quality of anesthesia recovery, postoperative cognitive function, postoperative pain, postoperative neurologic complications, as well as perioperative medical expense.

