## Methods

### Study purpose

(1) Primary purpose: To investigate neurologic function in the early postoperative period for patients with supratentorial intracranial gliomas under inhalational general anesthesia compared to intravenous general anesthesia. The hypothesis is that the difference in postoperative National Institute of Health Stroke Scale (NIHSS or modified NIHSS) score changes under the two general anesthesia methods are not different, with the score difference within − 1 to 1.

(2) Secondary purpose: To compare the effects of inhalational general anesthesia versus intravenous general anesthesia on neurocognition, hemodynamics, cerebral physiology, anesthesia recovery quality, pain scores, anesthesia expenses, and stress responses in patients with supratentorial intracranial gliomas undergoing elective craniotomy.

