### Study endpoint

The primary endpoint will be NIHSS score change within 4 h after general anesthesia by sevoflurane-remifentanil or propofol-remifentanil when observer’s assessment of alertness/sedation (OAA/S) reaches 4. The time to reach OAA/S score of 4 at the first time point will be recorded.

Secondary endpoints will be as follows:
The NIHSS score change at postoperative day 1 and postoperative day 2 from the baseline, the level of OAA/S in these two time points will be recorded.Hemodynamic stability including blood pressure, heart rate, episodes of hypertension, hypotension, tachycardia, and bradycardia;Intraoperative brain relaxation (Brain relaxation assessed immediately after opening of the dura on a scale ranging from 1 to 4 (1 = perfectly relaxed, 2 = satisfactorily relaxed, 3 = firm brain, 4 = bulging brain);Quality of anesthesia emergence including time of eye opening, time of emergence, coughing during extubation, postoperative nausea and vomiting (PONV), shivering, and agitation;Quality of anesthesia recovery assessed by QoR-40 at postoperative day 2;Changes of cognitive function at postoperative day 2 assessed by MMSE;Postoperative pain at PACU, 1, and 2 days after surgery evaluated by VAS;Postoperative neurological complications (e.g., intracranial hematoma, infection, seizure etc.);Anesthesia expenses and in-hospital total expenses;

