The 15-item National Institutes of Health Stroke Scale (NIHSS) was developed for and is widely used to evaluate neurologic function [20]. Although the modified NIHSS (mNIHSS) appears to be a more easily-used measure that is identical with the original NIHSS in its validation and reliability when evaluating the severity of stroke [21, 22], the deletion of limb ataxia in the mNIHSS has significance in patients with intracranial tumors based on our previous study [9], and there is no evidence showing the superiority of one to another in the intracranial tumor population. We therefore will choose to calculate both the NIHSS and the mNIHSS for comprehensive neurologic function evaluation. The Chinese version of NIHSS has been validated in a previous study [23].

Motor evoked potential (MEP) monitoring is very important for some supratentorial craniotomies if the tumor is located in or near the motor strip or descending motor pathways near the prefrontal cortex. Clinical evidence shows that sevoflurane suppresses MEP amplitudes in a dose-dependent manner [24, 25]. When using a sevoflurane-propofol combination in clinical practice, sevoflurane concentration is usually maintained below 0.4 MAC; while in this study, sevoflurane will be the only general anesthetic to maintain the desired anesthetic depth in the sevoflurane arm, the concentration will be much higher and vary among individual patients, resulting in failure of MEP monitoring. Therefore, patients who require intraoperative neurophysiological monitoring will be excluded from the study.

The current study aims primarily to elucidate the possible differential effect of inhalational sevoflurane versus intravenous propofol anesthesia on the short period of post-operative neurologic function in patients receiving supratentorial tumor resection in a randomized controlled trial. As the repeated neurologic function assessments are important to evaluate the patients’ recovery from surgical intervention and the presence of any complications, the results of this trial would help to interpret anesthetic residual effects on postoperative outcomes, and perhaps help to determine the intraoperative general anesthetic that affects neurologic function with the least detriment and therefore optimizes anesthetic management in this specific patient population.

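### The protocol names its primary variable in three incompatible ways: NIHSS alone, NIHSS or mNIHSS, and both scales

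*Protocol article*

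**What the plan says.** Five parts of the protocol article bear on which scale is primary.

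- **Outcomes:** on the ground that the two scales have not been compared in tumor patients, "we will score both as primary outcomes in this study".
- **Study purpose:** the primary hypothesis is written for either scale, with one margin: "NIHSS or modified NIHSS) score changes under the two general anesthesia methods are not different, with the score difference within − 1 to 1". It does not say how to choose between them.
- **Study endpoint:** "The primary endpoint will be NIHSS score change within 4 h after general anesthesia by sevoflurane-remifentanil or propofol-remifentanil", assessed when OAA/S reaches 4. The first secondary endpoint is "The NIHSS score change at postoperative day 1 and postoperative day 2 from the baseline". mNIHSS appears in neither list.
- **Abstract, Methods:** "The primary outcome will be neurologic function change assessed by National Institute of Health Stroke Scale (NIHSS) within 4 h after general anesthesia". mNIHSS enters only later: "Secondary outcomes will include NIHSS and modified NIHSS change 1 and 2 days after general anesthesia".
- **Sample size calculation and Statistical analysis plan:** the assumed difference, the between-group comparison and the confidence interval are all stated for NIHSS. mNIHSS is not mentioned.

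The Discussion says both scores will be calculated and does not rank them. It also remarks that "the deletion of limb ataxia in the mNIHSS has significance in patients with intracranial tumors based on our previous study".

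**The concern.** An equivalence claim should rest on one variable that is fixed before the data are seen. Here the same document supports three readings: NIHSS alone, either scale, or both. If the two scales disagree at the first postoperative assessment, the text could be cited for a positive or a negative primary result.

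The direction of the risk is particular to equivalence. A scale that omits some deficits may show a smaller difference between groups, and a smaller difference counts as success. The omitted items include level of consciousness and dysarthria, in a trial whose subject is residual anesthetic effect in the first hours after surgery. They also include limb ataxia, whose omission the authors themselves regard as important in these patients.

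**Working it through.** **1. Compare the statements.** The abstract and Study endpoint give NIHSS alone. Study purpose gives NIHSS or mNIHSS. Outcomes gives both. The abstract also makes mNIHSS secondary on days 1 and 2, while the secondary list in Study endpoint omits it. All of this is current text, so the conflict needs no calculation.

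**2. Compare the scales (Appendix, Table 3).** The NIHSS item maxima sum to 42. mNIHSS deletes items 1a (3), 4 (3), 7 (2) and 10 (2), and reduces the sensory item from a maximum of 2 to 1:

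42 − (3 + 3 + 2 + 2) − 1 = 31, which matches the stated total.

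mNIHSS therefore does not score 1a, facial palsy, limb ataxia or dysarthria. It still registers sensory loss as normal or abnormal, and it keeps the consciousness questions and commands (1b, 1c).

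**3. The plan's own sample size.** Inputs from Sample size calculation: difference 0.5, SD 1.5, margin 1.0, power 80%, stated n = 160 per group, raised to 176 for 10% drop-out.

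n = 2 × [1.5 × (z₁₋α + z₀.₈₀) / (1.0 − 0.5)]²

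- One-sided 0.025 (equivalence read from the 95% interval): 2 × [1.5 × (1.960 + 0.842) / 0.5]² ≈ 141.3, so 142.
- One-sided 0.05: 112.

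Neither gives 160. That is a separate matter, and this point does not depend on it. It does explain why the stated inputs give a single-scale power above 80% in the next step.

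**4. Power on one scale.** With 10% loss, 176 × 0.9 ≈ 158 per group are evaluable.

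- SE = 1.5 × √(2/158) = 0.1688
- k = (1.0 − 0.5)/0.1688 − 1.960 ≈ 1.00
- Power = Φ(k) ≈ 0.842

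**5. Two scales.** The documents give no SD, expected difference or correlation for mNIHSS. I assume the same SD, difference and margin as for NIHSS, bivariate normality, and a correlation ρ of 0.8 to 0.95, since mNIHSS is built from NIHSS items.

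- Either scale suffices, both true differences at the margin: error = 2 × 0.025 − Φ₂(−1.96, −1.96; ρ)
- Both scales must pass, both true differences 0.5: power = Φ₂(k, k; ρ)
- Split result: 2 × (single power − joint power)

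| ρ | Either-scale error (nominal 0.025) | Both-scales power | Split result |
|---|---|---|---|
| 0.8 | 0.039 | 0.781 | about 12% |
| 0.9 | 0.035 | 0.799 | about 9% |
| 0.95 | 0.032 | 0.812 | about 6% |

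**6. Sensitivity.** With independent scales the either-scale error would be 1 − 0.975² = 0.049; at ρ = 0.99 it would be 0.028. If equivalence were judged at one-sided 0.05 instead, the either-scale error would be 0.075 to 0.063 for ρ 0.8 to 0.95, and joint power at n = 160 would be 0.87 to 0.89.

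**The case against.** Most of the operative text points one way. The section headed Study endpoint, the abstract, the sample size and the analysis all use NIHSS, so a fair reader would take NIHSS as primary and treat the sentence in Outcomes and the "or" in Study purpose as loose wording. A multiplicity rule is also the kind of detail that a full protocol or analysis plan, not shown here, may contain. Both arguments stand as far as they go: they reduce the risk of selective reporting, and the absence of a multiplicity rule is not a finding. They do not remove the conflict, because a rule placed elsewhere would still leave this document with three answers to which variable is primary.

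A reader might also infer more than the documents support:

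- **That the error rate is seriously inflated.** Inflation needs an either-scale rule, which the analysis section does not state, and true differences at the margin on both scales. Under the correlations assumed it is modest.
- **That requiring both scales would leave the trial underpowered.** The plan promises 80%. The 84% in step 4 is a recalculation from the stated inputs, and 78–81% for both scales lies close to the promise.
- **That mNIHSS is blind to every altered item.** It loses severity grading on the sensory item, not detection, and part of the consciousness assessment remains.
- **That ±1 is easier to meet on mNIHSS by an amount that follows from 31 versus 42 points.** Scale maxima say little about small changes in patients enrolled with a Glasgow score of 15, and no mNIHSS SD or difference is given. The loss of sensitivity is real in direction; its size is unknown.

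**Conclusion.** The contradiction holds, and it concerns the variable on which the trial's main claim rests. Its clearest practical consequence is that the "or" in Study purpose would permit an equivalence claim on the less sensitive scale. The numerical consequences are secondary: a one-sided error of about 3.2–3.9% instead of 2.5% if either scale suffices, or no inflation and about 78–81% power if both must pass. These figures rest on equal SDs, differences and margins, on correlations of 0.8 to 0.95, and on judging equivalence by the 95% interval. The contradiction itself rests on none of these assumptions. It should be settled before outcome data are examined by group, because a later choice of scale could follow the result.

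**What to change.** In Study purpose and Outcomes, name NIHSS change from baseline as the single primary endpoint. Keep the definition in Study endpoint: within 4 h after general anesthesia, when OAA/S reaches 4. A looser phrase such as the first postoperative assessment would lose both conditions. This agrees with the abstract, Study endpoint, Sample size calculation and Statistical analysis plan.

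In Study endpoint, list mNIHSS change at the same time point, day 1 and day 2 as a secondary, supportive analysis, and state that it cannot replace the NIHSS result.

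If two primary scales are truly intended, the document would instead need a both-must-pass or error-splitting rule, a justified mNIHSS margin and a matching sample size.

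The recommended change costs wording only; data, visits and sample size are unaffected. Trial status gives a recruitment start of May 28th, 2018, so the change may need ethics approval and a registry update under Protocol amendment.
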